### Study design

This is a sequential mixed-method study consisting of a randomised double-blind controlled trial and an exploratory qualitative study. The study implementation protocol is outlined in Figure 1. A research assistant (RA1) will recruit eligible participants from the cardiac clinics and wards of four regional hospitals in Hong Kong. The study sites are leading hospitals providing cardiac care services within the region. He/she will collect participants' baseline (T0) demographic data and study variables during a face-to-face interview. Block randomisation with a block size of 8, 10 or 12 will be used to ensure even distribution of participants between the two study groups. The block size and the respective allocation sequence to the intervention group receiving a modelling-based narrative intervention (by RA1) and control group receiving a didactic education (by RA2), will be determined by a computer-generated sequence. Participants chronologically recruited to the study will be allocated to the study groups by RA1 according to the computer generated sequence. Another independent RA (RA3), who is blinded to the study group allocation, will collect the post-intervention data. To detect short-term and long-term intervention effects, the outcome variables will be measured repeatedly at 3 (T1), 12 (T2) and 24 (T3) months following baseline data collection for both study groups. This extended period of outcome evaluation permits the study to detect the intervention effects on participants' actual care-seeking behaviours. Previous studies indicated that approximately 16% of these patients experienced AMI symptoms within two years. In the data collection telephone calls, the RA3 will enquire about whether the participants have been admitted to an emergency department with the experience of AMI symptoms. The study participants and their next of kin are strongly advised to contact the RA if they have been admitted due to a possible AMI attack.

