### Study participants

Patients will be eligible to join the study if they are (1)  $\geq 18$  years of age, (2) living in the community, (3) with a confirmed diagnosis of a prior AMI attack, (4) consent to participate and (5) those who can read Chinese. Individuals who do not understand Cantonese, with impaired communication ability, psychiatric problems or impaired cognitive functioning (i.e. Abbreviated Mental Test  $\leq 6$ ) which may hinder participation in the interventional activities will be excluded. For the RCT study, the sample size is determined on the basis of a large-scale RCT examining the effect of a brief nursing educational intervention on care-seeking knowledge, attitudes and beliefs related to AMI in people with CAD. The effect sizes for knowledge, attitudes and beliefs were 0.39, 0.24 and 0.23 at 3 months after the intervention. In consideration of both clinical relevance and previous study findings, the sample size of this study is determined to give the study adequate power to detect at least a small to medium effect size on the primary outcomes. Using PASS 13 (NCSS, Kaysville, USA), it is estimated that a sample size of 252 subjects per study arm would give the study 80% power at 5%

level of significance to detect an effect size as small as 0.23 on our primary outcomes between the control and intervention arms at the post intervention time points. Further allowing for a potential dropout rate of up to 20%, a total of 315 subjects per arm will be recruited. For the qualitative phase, a criterion sampling of 30 participants who have received the modelling-based narrative intervention will be invited to join on the basis of their prehospital delay time, which will be categorised into three groups:  $\leq 2$  hours,  $> 2$  and  $\leq 6$  hours, and  $> 6$  hours. The criterion is set according to the international AMI management guidelines, where such cut-offs are used to categorise patients into early, intermediate and late responders. A total of 30 participants will be recruited, with 10 participants for each category. Maximum variations in the sociodemographic and clinical profile of the participants will also be adopted in the sampling procedure to illustrate a wider range of data.

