#### Outcome measures

The Acute Coronary Syndrome Response Index (ACSRI-C, Chinese version) will be used to measure the knowledge of AMI symptoms, care-seeking beliefs and attitudes upon symptoms occurrence. The knowledge subscale consists of 21 items to be responded dichotomously (yes/no). A four-point Likert scale is used to respond to the attitudes (5 items) and beliefs subscales (7 items). Higher scores indicate better knowledge, more appropriate care-seeking attitudes and beliefs. The ACSRI-C has good reliability (Cronbach's alpha = .81), convergent and construct validity.

The use of ambulance is defined as the primary means of selecting an ambulance as the transportation modality to hospitals. It will be retrieved from medical records and doubly confirmed with the participants.

The prehospital delay time is defined as the time interval between onset of acute symptoms and the documented time of arrival at a hospital's emergency department. The time of symptom onset will be elicited by patients' recall. To ensure its accuracy, a validated benchmarking technique in which the time of symptom onset is placed in the context of routine events that surround symptom onset will be used. The hospital arrival time will be retrieved from the patient's medical record.

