#### Data analysis

For the RCT study, data analysis will be performed on an intention-to-treat basis. Baseline characteristics between the two study arms will be compared by t-test, chi-square or Fisher's exact test

where appropriate. A generalized estimating equation (GEE) model will be used to compare the differential changes on the outcomes across the time points T0, T1, T2 and T3 between the two study arms with adjustment for potential confounding variables. Baseline characteristics with p values < 0.25 for between-group difference will be considered as potential confounding variables. GEE model can account for intra-correlated repeated measures data and accommodate missing data caused by incomplete visits or dropout, provided that the data are missed at random, and thus are particularly suitable for intention-to-treat analysis without the need of imputation for missing data. All statistical analyses will be performed using IBM SPSS 23.0. All statistical tests will be two-sided and a p-value < 0.05 will be considered statistically significant. For the qualitative study, the audio-taped data will be transcribed verbatim. The investigation team will ensure accuracy of the transcription by cross-checking. Content analysis will be adopted to code the qualitative data on participants' perceptions and acceptability of the modelling-based narrative intervention. The analysis will also seek to understand why and how the study intervention influences patients' care-seeking behaviours. The codes units will be organised into categories and subcategories, which will be analysed for emerging themes. The trustworthiness of the qualitative analysis will be enhanced by audio-taping of the interviews, conducting an audit trail, involving two team members to code the qualitative data independently.

**Figure 1.** Study implementation protocol

[figure not shown]

**Figure 2.** Graphical presentation of the modelling-based narrative intervention protocol

[figure not shown]

**Table 1.** The storyline of the narrative video-based virtual heart attack experiencing session

**Background information of the model patient:** **[name]**, 58 year-old man, bus driver, non-smoker, with hypertension and hyperlipidaemia. He sustained a musculoskeletal injury over his chest region a week ago

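### After baseline, prehospital delay and ambulance use are defined only for the at most 16% or so who go to hospital with AMI symptoms, yet the protocol gives them the all-participant T0–T3 GEE as intention-to-treat

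*Protocol*

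**What the plan says.** All places are in the Protocol.

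- **Research plan and methodology.** Care-seeking beliefs and attitudes are primary. Knowledge, ambulance use and prehospital delay are secondary. The hypothesis covers all five at 3, 12 and 24 months.
- **Outcome measures.** Delay is "defined as the time interval between onset of acute symptoms and the documented time of arrival at a hospital's emergency department". Ambulance use is the mode of transport to hospital, taken from medical records and confirmed with the participant.
- **Study design.** The long follow-up is justified thus: "This extended period of outcome evaluation permits the study to detect the intervention effects on" actual care-seeking behaviour. The next sentence says that "approximately 16% of these patients experienced AMI symptoms within two years". Events come to light through the blinded assessor's telephone calls. In addition, participants and next of kin "are strongly advised to contact the RA if they have been admitted due to a possible AMI attack".
- **Study participants.** The sample size is argued for the primary outcomes only: "a sample size of 252 subjects per study arm would give the study 80% power at 5" per cent significance, "to detect an effect size as small as 0.23 on our primary outcomes". With 20% dropout this becomes 315 per arm. No power is stated for delay or ambulance use.
- **Data analysis.** The analysis is by intention to treat. One GEE model will "compare the differential changes on the outcomes across the time points T0, T1, T2 and T3 between the two study arms". No outcome is excepted. The section argues that no imputation is needed, because GEE tolerates data lost through missed visits or withdrawal if they are missing at random.

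**The concern.** A delay or a mode of transport exists only if there was a journey to hospital. The model named for the outcomes compares change over four fixed visits in everyone randomised, which suits a questionnaire score but not an outcome triggered by an event.

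Three consequences follow if the text is applied as written.

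1. **Undefined is treated as missing.** A participant with no event has no delay to be missing. The stated justification covers missed visits and withdrawal, so it does not reach this case.
2. **The comparison is not of the randomised groups.** It is confined to those who present, and presentation occurs after randomisation. The intervention teaches symptom recognition, risk identification and overcoming barriers to seeking care, so it may change who presents. Randomisation no longer guarantees that the two subsets are alike.
3. **The detectability statement is not supported for modest effects.** It stands next to an event rate that leaves few participants to analyse.

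At stake is how a reported difference, or lack of one, in actual behaviour can be read. These outcomes are part of the trial's first aim and hypothesis.

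**Working it through.** **Inputs from the protocol.** 252 evaluable and 315 recruited per arm; 20% dropout; two-sided 5% ("All statistical tests will be two-sided and a p-value < 0.05 will be considered statistically significant"); effect size 0.23 for the primary outcomes; about 16% with AMI symptoms in two years; up to 50% of Hong Kong patients not using an ambulance (Background).

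**Assumptions added here.** The 16% applies in both arms; every symptomatic participant reaches hospital; one event each; 50% ambulance use in the control arm; no clustering by intervention group. The 0.23 SD is borrowed from the beliefs outcome, because the protocol gives no effect size for delay.

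**Step 1: the protocol's own figure.** For two means, n per arm = 2(1.960 + 0.842)²/d². With d = 0.23 this gives 297, not 252. At 252 per arm, power is Φ(0.23·√(252/2) − 1.960) = Φ(0.62) = 73%. The figure 252 matches d = 0.25. It matches d = 0.23 only with inputs that are not stated, such as a baseline correlation of about 0.39 in an adjusted analysis. The dropout step does reproduce: 252/0.80 = 315. Nothing below depends on this mismatch.

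**Step 2: participants with a post-baseline value.**
- All recruited: 0.16 × 315 = 50.4 per arm (101 in total).
- After dropout: 0.16 × 252 = 40.3 per arm (81 in total).

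These are upper figures given the 16%, because that rate counts people with symptoms, not arrivals at an emergency department.

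**Step 3: delay.** With m participants per arm, the detectable effect at 80% power is 2.802·√(2/m), and power at 0.23 SD is Φ(0.23/√(2/m) − 1.960).

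| | m = 50.4 | m = 40.3 |
|---|---|---|
| √(2/m) | 0.199 | 0.223 |
| Detectable effect, normal approximation | 0.56 SD | 0.62 SD |
| Detectable effect, t-test (50 and 40 per arm) | 0.57 SD | 0.63 SD |
| Power at 0.23 SD, normal approximation | 21% | 18% |
| Power at 0.23 SD, t-test | 21% | 17% |

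The unit is the SD of delay, or of log delay if it is analysed on that scale. The protocol gives no SD for delay, so these cannot be turned into minutes.

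**Step 4: ambulance use.** Power = Φ{[(p₂ − p₁)√m − 1.960·√(2p̄(1 − p̄))]/√(p₁(1 − p₁) + p₂(1 − p₂))}, where p̄ is the mean of the two proportions and p₁ = 0.50.

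| Intervention arm | Power, m = 50.4 | Power, m = 40.3 |
|---|---|---|
| 60% | 17% | 14% |
| 70% | 54% | 45% |
| Rate needed for 80% power | 76.6% | 79.4% |

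An arcsine calculation gives 77% and 80% for the last row.

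**Step 5: what 0.23 SD would need.** About 297 participants with events per arm, so 297/0.16 ≈ 1,856 randomised per arm, against 315 planned.

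**Step 6: the missing-data argument.** About 100% − 16% = 84% of participants would have no post-baseline value even if every visit were completed. Perfect retention would not change that, so it is not the kind of loss that the missing-at-random argument describes.

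**The case against.** The strongest reply is that these are secondary outcomes, that no power is claimed for them, and that the sentence on detection only explains why follow-up is long, with the 16% openly stated next to it. Much of that stands: there is no wrong power figure here. A reader might infer that the protocol promises adequate power for behaviour, but the text does not say so. What remains is that the sentence, beside 16%, is not supported for modest effects.

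It can also be said that the Data analysis section does not name these two outcomes and that details may sit in an analysis plan. Leaving details for later would be no fault. But the section states one model for the outcomes without exception, labels it intention-to-treat and gives a missing-data reason that does not fit. An analysis plan could mend this only by departing from the protocol.

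Every participant has had an AMI, so a T0 delay and transport mode could exist for all. The protocol does not say that they are collected, and they would not supply values at T1 to T3.

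Some stronger readings are tempting but not supported:

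- **Bias in favour of the intervention.** Extra early visits for mild symptoms would shorten delay in that arm, but drawing in people with atypical symptoms could add late presenters. The direction is unknown.
- **Unequal finding of events.** The arms differ in contact time, and events are first flagged by report. But a blinded assessor asks both arms the same question, and arrival time and transport come from records. Unequal ascertainment is possible, not shown.
- **Conflicting event definitions.** The wording varies, but the phrase about a possible attack tells people when to telephone and does not define an outcome. One definition is still needed.
- **Worst ranks for symptomatic non-attenders.** The calls ask about emergency department admission, so non-attenders are not identified. Ranking only symptomatic people would still not restore intention-to-treat.

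**Conclusion.** The point holds for the two behaviour outcomes and does not touch the primary ones. As written, the protocol puts outcomes that at most about 16% of participants can have into an all-participant repeated-measures model. It also describes the result as intention-to-treat under an assumption that does not cover undefined values. The resulting comparison is conditional on presenting to hospital and may be biased either way.

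With 40 to 50 participants per arm, only large effects are detectable at 80% power: about 0.56–0.63 SD in (log) delay, or a rise in ambulance use of roughly 26 to 30 percentage points from 50%. Power at 0.23 SD is about 18–21%. These sizes rest on the assumptions listed with the calculation. The 50% is the least secure of them, because the protocol says up to 50% did not use an ambulance and controls here also receive education. Fewer arrivals than 16%, or clustering by group, would make detection harder.

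**What to change.** 1. **Data analysis.** Except prehospital delay and ambulance use from the T0–T3 GEE and from the intention-to-treat and missing-at-random statements.
2. **Separate analysis.** Use the first qualifying emergency department presentation per participant, under one event definition. Compare delay on the log scale or by ranks, and ambulance use by logistic regression. State that both are conditional on presentation and are not intention-to-treat.
3. **Report over all randomised, by arm,** the proportion with an emergency department presentation and the proportion with confirmed AMI. These keep the randomised denominator and show whether the intervention changed who presents. Show the number with unknown status in each arm.
4. **Study design.** Reword the sentence on detecting behaviour effects so that these outcomes are exploratory, and give the detectable effects with their assumptions.

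**Cost.** Changes of wording and analysis, plus recording whether AMI was confirmed for each presentation. Medical records are already consulted for arrival time and transport. The downside is a weaker claim for the behaviour outcomes.

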### (a) Background of research

#### The importance of timely care-seeking in the context of AMI

Acute myocardial infarction (AMI) is the acute and severe manifestation of coronary artery disease (CAD), resulting from a sudden cessation of coronary blood flow due to thrombotic occlusion. It is an emergency requiring immediate medical attention. The amount of myocardial necrosis from the moment of occlusion is curvilinear with a greater extent of cell death occurring in the early hours. In addition, the efficacies of reperfusion therapies are also highly time-dependent. Despite the types of reperfusion strategies, their efficacies diminish over time with a striking benefit observed within the first 2 hours of symptom onset. For instance, using an analysis of 22 trials, the researchers documented a substantial reduction in mortality when the thrombolytic drugs were administered within 2 hours of symptom onset. Likewise, De Luca et al. reported that the risk of 1-year mortality was raised by 7.5% for every 30-minute delay in receiving the percutaneous coronary intervention. Other than the ischaemic effect, AMI patients are prone to develop fatal arrhythmias in the early hours of disease onset. According to the latest statistics, majority of AMI-related deaths occur in the first hour of symptom onset are related to ischaemia-induced ventricular arrhythmias, which accounts for up to 70% of the CAD-related deaths. For this reason, early access to emergency medical care for prompt defibrillation and cardiopulmonary resuscitation is of paramount importance for AMI patients. Moreover, using ambulance for transporting to hospitals enables patients to get immediate emergency care from paramedic if fatal arrhythmia occurs. In Hong Kong, up to 50% of the patients did not use ambulance during an AMI attack, which greatly jeopardize their chance of survival. Indeed, AMI survivors are prone to have recurrent events and high mortality risk. A representative trial reported that up to 54% of patients presented with new myocardial ischaemia within the first year of AMI, while another large population trial showed a 17.4% of 1-year risk of re-infarction. Given that the time taken by patients to make their care-seeking decisions accounts for the major portion of the total ischaemic time and the high recurrent rates among the AMI survivors, there is a pressing need to develop effective interventions to promote timely care-seeking in AMI patients.

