#### **(b) Research plan and methodology**

The aim of the study is two-fold: i) to evaluate the effects of a modelling-based narrative intervention on care-seeking beliefs, attitudes and knowledge, use of ambulance and prehospital care-seeking delays among AIM patients, and ii) to explore how and why the intervention affects the care-seeking behaviours from the patients' perspective. The behavioural intention, as reflected by the care-seeking beliefs and attitudes, are the primary outcomes, while AMI knowledge, use of ambulance and prehospital delays in care-seeking in AMI attacks are the secondary outcomes. The research hypothesis

of the first aim is that AMI patients who receive the modelling-based narrative intervention will report better changes in: i) care-seeking beliefs, ii) care-seeking attitudes, iii) AMI-related knowledge, iv) more likely to use ambulance, and v) shorter prehospital delays when AMI symptoms occur at 3, 12, and 24 months after the intervention, than those who receive didactic education on AMI care-seeking.

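### Prehospital delay and ambulance use are found and defined only for participants who reach an emergency department, so these secondary comparisons rest on a subset that the intervention can change

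*Protocol*

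**What the plan says.** The hypothesis in the protocol's section (b), Research plan and methodology, predicts more ambulance use and "shorter prehospital delays when AMI symptoms occur at 3, 12, and 24 months after the intervention". Both are secondary outcomes; care-seeking beliefs and attitudes are primary.

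Study design describes two ways of finding events, and both depend on admission. In the follow-up calls the blinded assistant will "enquire about whether the participants have been admitted to an emergency department with the experience of AMI symptoms". Participants and next of kin are "strongly advised to contact the RA if they have been admitted due to a possible AMI attack".

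Outcome measures then defines the outcomes in terms of arrival:

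- Delay is "the time interval between onset of acute symptoms and the documented time of arrival at a hospital's emergency department", and for its starting point: "The time of symptom onset will be elicited by patients' recall".
- Ambulance use is "the primary means of selecting an ambulance as the transportation modality to hospitals", with this source: "It will be retrieved from medical records and doubly confirmed with the participants".

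Neither section describes a question about symptoms that did not lead to attendance, or the collection of deaths before arrival. Data analysis applies generalised estimating equations (GEE) on an intention-to-treat basis, relying on data missing at random.

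**The concern.** The intervention is built to change whether people go to hospital. Study interventions lists symptom recognition and perceived barriers among the session topics. In Table 1 the third video pause falls where the model patient is deciding whether to go at all, and the fourth where he chooses between ambulance and taxi. If the intervention succeeds, the two arms can contribute different kinds of participant to the attender group. One arm may include people who would otherwise have stayed at home, and people who come in for what proves not to be AMI. Randomisation does not protect a comparison within such a group.

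GEE under missing at random does not repair this. In the data as collected, someone who had symptoms and stayed at home looks the same as someone who had none. Deaths before arrival are also left out, although the background section says that the "majority of AMI-related deaths occur in the first hour of symptom onset are related to ischaemia-induced ventricular arrhythmias".

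At stake is how the two behavioural secondary outcomes are read: an improvement in attendance could appear as no effect, or as longer delay, among those who attended.

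**Working it through.** **The plan's own figures.** The protocol states no event count or power for delay or ambulance use; its sample size concerns the primary outcomes. It does give 16% of such patients experiencing AMI symptoms within two years (Study design) and 315 recruited per arm, 252 after 20% dropout (Study participants).

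- 0.16 × 315 = 50.4, about 50 symptomatic participants per arm
- 0.16 × 252 = 40.3, about 40 per arm if only 252 are retained

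This treats the 16% as everyone with symptoms, whether or not they attended. That is an assumption.

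**Illustration 1: arrival within 2 h.** Assumed: 50 symptomatic per arm; x of them never attend in control; 20 in each arm arrive within 2 h; the intervention brings in all x, every one later than 2 h. Among attenders, control is 20/(50 − x) and intervention is 20/50.

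| x | Control | Intervention | Apparent deficit |
|---|---|---|---|
| 5 | 20/45 = 44.4% | 40.0% | 4.4 points |
| 10 | 20/40 = 50.0% | 40.0% | 10.0 points |
| 15 | 20/35 = 57.1% | 40.0% | 17.1 points |

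Over all randomised participants, with x = 10:

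- arrived within 2 h: 20/315 = 6.3% in both arms
- attended: control 40/315 = 12.7%, intervention 50/315 = 15.9%, a gain of 3.2 points

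The deficit disappears and the gain in attendance shows.

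**Illustration 2: less extreme inputs.** Assumed: a share h of symptomatic control participants do not attend; the intervention brings in half of them.

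*Mean delay.* Control attenders average 4 h; those who would attend anyway shorten by a fraction f; new attenders arrive at L hours. Intervention mean = [(1 − h) × 4 × (1 − f) + 0.5h × L] / [(1 − h) + 0.5h].

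- h = 20%, f = 10%, L = 12: (2.88 + 1.20)/0.90 = 4.53 h, against 4.00 h
- h = 10%, f = 20%, L = 8: (2.88 + 0.40)/0.95 = 3.45 h, a difference of −0.55 h
- h = 30%, f = 0, L = 24: (2.80 + 3.60)/0.85 = 7.53 h, a difference of +3.53 h

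The last two are the ends of the range tried (h 10–30%, f 0–20%, L 8–24 h).

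*Arrival within 2 h.* h = 20%, rising from 40% to 45% in those who would attend anyway, new attenders all late. Observed: 40.0% v (0.8 × 0.45)/0.9 = 40.0%. Over all symptomatic participants: 0.8 × 0.40 = 32% v 0.8 × 0.45 = 36%. A real gain appears as none.

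*Ambulance use.* h = 20%, unchanged at 50% in those who would attend anyway.

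- 20% of new attenders use an ambulance: observed 50.0% v (0.40 + 0.02)/0.90 = 46.7%, while use over all symptomatic participants rises from 40% to 42%
- 80% of new attenders do: observed 50.0% v (0.40 + 0.08)/0.90 = 53.3%, the correct direction

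**Precision (x = 10, normal approximation).**

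- Attenders: standard error √(0.5 × 0.5/40 + 0.4 × 0.6/50) = 10.5 points around a 10-point deficit
- Attendance over all randomised: √(0.127 × 0.873/315 + 0.159 × 0.841/315) = 2.8 points around a 3.2-point gain

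Neither would be statistically significant alone. The issue is bias in the estimate and how it is read.

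**The case against.** The strongest reply is that nothing here is inconsistent: delay to arrival and mode of transport exist only for people who reach hospital, so asking about admissions matches the outcomes as defined, and attendance is not a listed outcome. That is right as far as it goes. A reader might infer that the case-finding question contradicts the definitions; it does not. What stands is that the hypothesis is about behaviour when symptoms occur, and the defined outcomes answer it only for those who arrived.

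A reader might also infer that the unrecorded episodes leave the behavioural aim beyond rescue by any analysis. Illustration 1 shows otherwise: with all randomised participants as the denominator, data already planned give 20/315 in both arms for early arrival and 40/315 v 50/315 for attendance. The choice of denominator may also be settled in a statistical analysis plan that is not shown.

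Three further points hold. The protocol gives no full call script and Figure 1 is not shown, so the calls may ask more than is described. Illustration 1 uses extreme inputs: every non-attender converted, all late, and no improvement in anyone else. And the death argument has no size: the background statistic is a share of coronary deaths, not a rate in this cohort, and a death in the first hour need not reflect delay.

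Finally, replacing attenders by self-reported symptom episodes would not remove the problem. The intervention teaches symptom recognition, so the number of episodes reported could itself differ by arm.

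**Conclusion.** The concern holds for two secondary outcomes. As described, prehospital delay and ambulance use are compared among people selected after randomisation by a behaviour that the intervention targets, and the result may be biased in either direction. Under the assumptions of Illustration 1, an intervention that only adds late attenders would show an apparent deficit of about 4 to 17 points in arrival within 2 h. Over the range tried in Illustration 2, the observed difference in mean delay runs from −0.55 h to +3.53 h. Non-attendance, conversion and arrival times are all assumed, because the protocol gives none of them.

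A reader might infer that an effective intervention will look ineffective or harmful. The documents do not support that: with few non-attenders, or a large effect in those who would attend anyway, the observed direction stays correct. Nor is the primary result in doubt, since beliefs and attitudes do not depend on having an episode. The change is worth making because it is cheap and the extra data cannot readily be collected afterwards.

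**What to change.** **Analysis.** Keep delay and ambulance use among attenders, labelled descriptive, with the number of attenders by arm. Add three comparisons over all randomised participants by arm: attended with suspected AMI, attended within 2 h, and attended by ambulance. Count death before arrival as not attended.

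**Data collection.** In the existing T1–T3 calls, also ask whether AMI-type symptoms occurred without attendance and what was done. Record out-of-hospital cardiac deaths from next of kin or records. From the medical record already retrieved, code each attendance as confirmed AMI or not. Report all of these by arm as supportive data.

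**Cost.** A few extra questions, one extra field, and some follow-up of deaths. Unattended episodes are self-reported and unconfirmed, and their reporting may differ by arm, so they should not become the main denominator. The all-randomised comparison is diluted, since on the protocol's 16% about 84% of participants would have no symptoms. It also needs attendance to be established for participants who drop out, for whom the protocol allows up to 20%.
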